### Data collection

#### Survey data

The screener questionnaire will be administered online via the study website. The baseline and Months 6, 12, 18, and 24 questionnaires will be provided to participants through unique, personal Qualtrics™ (Qualtrics International Inc., Provo, UT, USA) links sent via email. All questionnaires will contain questions to assess secondary outcomes, including the DSMQ, GPAQ, PSQI, a modified WPAI:SHP, and 5-level EQ-5D survey instruments, as well as the Brief Illness Perception Questionnaire (BIPQ), which has been validated in English for diabetes [34, 35]. Additionally, the baseline questionnaire includes questions on socioeconomic characteristics, while the follow-up questionnaires include questions on program evaluation.

#### Health outcomes

Measurements for health outcomes will be recorded at the training session (baseline) and at the Months 6, 12, 18, and 24 follow-up assessments conducted at Duke-NUS Medical School (or other study venues, if available). HbA_1c_ tests will be conducted using the high-performance liquid chromatographic method via the VARIANT™ II TURBO Hemoglobin Testing System (Bio-Rad Laboratories Inc., Hercules, CA, USA) on the blood samples collected at all study visits. No blood samples will be stored after the HbA_1c_ tests have been completed. Height (Seca 217 Mobile Stadiometer; Seca GmbH, Hamburg, Germany) will only be measured at baseline. Weight (Seca 869 Mobile Floor Scale; Seca GmbH, Hamburg, Germany) and blood pressure (Welch-Allyn 420 Spot Vital Signs BP Monitor; Welch Allyn, Skaneateles Falls, NY, USA) will be measured at all study visits. For height and weight, duplicate measurements will be recorded, along with a third measurement if the first two readings are unequal. For systolic and diastolic blood pressure, measurements will be taken after a period of rest of at least 5 min. Three readings will be taken with 3-min intervals of rest between each measurement, and the average of the last two readings will be used.

#### Study devices and apps

Participants in the two intervention arms will wirelessly sync data from their pedometer, glucometer, and pill tracker with their anonymous Fitbit™, Glyco, and DoseSmart™ study accounts, respectively. Weight logs and quiz scores captured on the Glyco app will be stored in participants’ Glyco accounts. In order to display updated participant activities and M-Points on the M-POWER app, the study platform will pull data from all the anonymous study accounts on a daily basis via API and automatically calculate and award M-Points daily.

#### Data for sensitivity analysis and cost-effectiveness analysis

Medical data such as HbA_1c_ test results taken during usual care at the clinics and diabetes medications prescribed and purchased, including insulin initiation dates, will be obtained from the medical records and pharmacy bills of all participants. HbA_1c_ test results from these medical records will be used in sensitivity analyses. Billing data from inpatient, outpatient, pharmacy, and emergency departments will be collected to estimate net costs and cost offsets for the cost-effectiveness analysis. The costs of program delivery will be determined by capturing data on all relevant (non-sunk) labor costs, materials and supplies, contracted services (including costs for GlycoLeap), and M-POWER Rewards payouts.

### Data management and monitoring

During the study, all data will be stored on secure servers at Duke-NUS Medical School and will be backed up daily. All data containing personal identifiers will be encrypted with password protection. All physical research data, including consent forms, data entry forms, and password-protected portable hard disk drives containing backup data, will be stored in locked cabinets at Duke-NUS Medical School. Only de-identified data will be shared with statisticians for data analysis, and only the investigators and study team directly involved with the study will have access to the data. The research data will be kept for at least 10 years after research completion and securely destroyed upon the publication of all pertinent research studies or reports.

A Data and Safety Monitoring Board (DSMB) with members who are external to the study team and independent of the study and sponsor has been established to oversee matters on participant data security, participant safety, and implementation fidelity. Members consist of two consultant endocrinologists, a biostatistician, and the head of Duke-NUS Medical School’s information technology department. The DSMB charter will be made available upon request. No termination guidelines or rules have been defined for this study.

This study is subject to reviews and/or audits by the SingHealth Research Quality Assurance Unit. These reviews or audits may be conducted routinely, triggered by the SingHealth CIRB, or upon an investigator’s request.

#### Survey data

Each completed screener questionnaire attempt will generate a unique ID that will be traceable to individual prospective participants. Similarly, each personal Qualtrics™ link for baseline and follow-up questionnaires will contain the participant’s unique study ID, ensuring that we can differentiate survey entries completed by different participants. Data validation will be implemented to ensure that responses are provided for all questions and that questionnaire entries are only flagged as complete after the participant reaches the end of the questionnaire. For the baseline questionnaire, if a participant completes the same questionnaire more than once by mistake, each entry will be recorded separately and timestamped, allowing us to assess the multiple entries. Only one entry from each participant will be used for data analysis. For the follow-up questionnaires, participants will only be permitted to complete each questionnaire once. Survey data from all questionnaires will be downloaded by the study team regularly and checked for completion and any errors or inconsistencies.

#### Health outcomes

Measurements taken at the study visits will be recorded on hardcopy printouts. All data will be converted into electronic data using double data entry by two different individuals and verified for consistency. Any discrepancies will be resolved by referring to source documents. At the study visits, phlebotomists will verify participants’ identities before drawing blood and will label blood samples with the participants’ study IDs only. HbA_1c_ results will not contain any personal identifiers and will be shared with the study team after each batch of blood samples is processed.

#### Study devices and apps

To encourage participants in the incentive arms to engage with the study components, weekly inactivity notifications that list the components that they have not been engaging with will be emailed to participants. Participants who are not engaging with the study components will be contacted by the study team, who will offer their assistance and ensure that participants are not experiencing problems with the devices or apps. Study team members will also note those who indicate that they do not wish to perform any activity(s) and will not contact these participants for the purpose of troubleshooting. At each follow-up assessment, study team members will also verify that participants are using the devices as instructed and respond to any queries that participants might have on usage of the devices or apps. Besides the aforementioned measures to reduce data loss, participants in both intervention arms will be incentivized to upload their data: participants will be given SGD2 per device per month for syncing their pedometers, glucometers, and pill trackers with their anonymous study accounts see (Table 3).

As participants in the DMP plus M-POWER arm may be tempted to cheat in order to earn more M-Points, they will sign a participant oath at the end of the training session and each time they collect their M-Points redemption payouts. This might help to improve data validity, as such oaths could reduce the likelihood of cheating [24]. The study team will also manage and back up data from the devices and apps and regularly check the data for inconsistencies that may suggest cheating.

### Statistical methods

#### Preliminary descriptive analyses

Preliminary descriptive analyses will be performed, and the patterns of missing data/drop-out rate in each arm will be examined. The statistician conducting the analysis will be blinded to the arm assignments when conducting preliminary descriptive analyses. The arm assignments will be disclosed only after the final database lock. A detailed statistical analysis plan will be prepared before the final database lock.

#### Primary analysis

Mean change in HbA_1c_ level at Month 12 is the primary outcome. The primary analysis will be performed on a modified intention-to-treat population, including participants who have both baseline and Month 12 HbA_1c_ level data. A linear regression model with HbA_1c_ level at Month 12 as the dependent variable and an intercept, HbA_1c_ level at baseline (continuous variable), indicator variables for participants who received DMP alone and participants who received DMP plus M-POWER, and indicator variables for stratification factors (gender and diabetes center) as independent variables will be performed. Using this model, a test for the global null hypothesis of all three arms having equal mean HbA_1c_ level at Month 12 will be performed (Null Hypothesis 1: Coefficient of DMP plus M-POWER = Coefficient of DMP = 0), followed by tests for three pairwise hypotheses, comparing mean HbA1c level at Month 12 in DMP alone vs. usual care (Null Hypothesis 2: Coefficient of DMP = 0), DMP plus M-POWER vs. usual care (Null Hypothesis 3: Coefficient of DMP plus M-POWER = 0), and DMP plus M-POWER vs. DMP alone (Null Hypothesis 4: Coefficient of DMP plus M-POWER = Coefficient of DMP). We will also conduct a sensitivity analysis with further adjustment for dichotomized HbA1c levels at baseline (7.5–9.2% vs. 9.3–11.0%). The differences in the primary outcome between study arms will be presented along with corresponding 95% confidence intervals. Following the closed testing procedure [32] for controlling for multiple comparisons involving three groups, only if tests of both the global null hypothesis and a pairwise null hypothesis reach statistical significance at the 0.05 level will the pairwise null hypothesis be rejected.

If there are substantially different drop-out rates or different drop-out patterns among the three arms, a general linear model for repeated measures will be performed for the primary analysis. This model simultaneously models HbA_1c_ level at baseline, Month 6, and Month 12 as the dependent variables and includes interactions between indicator variables for DMP alone and Month 6 visit, DMP plus M-POWER and Month 6 visit, DMP alone and Month 12 visit, and DMP plus M-POWER and Month 12 visit as independent variables. The model will also adjust for visit (indicator variable for the Month 6 visit and indicator variable for the Month 12 visit) and randomization stratification variables (gender and diabetes center). An unstructured matrix will be used to model the residual variance-covariance structure within participant. The model does not include main effect terms for the intervention variables, and thus it constrains the estimated group means of baseline HbA_1c_ levels to be identical across the three randomized groups. This model specification helps control for the variation in baseline HbA_1c_ level arising by chance among the randomized groups. Using this model, a test for the global null hypothesis of all three arms having equal mean HbA_1c_ level at Month 12 will be performed (Null Hypothesis 1: Coefficient of interaction between indicator of DMP alone and indicator of Month 12 visit = Coefficient of interaction between indicator of DMP plus M-POWER and indicator of Month 12 visit = 0), followed by tests for three pairwise hypotheses, comparing mean HbA_1c_ level at Month 12 in DMP alone vs. usual care (Null Hypothesis 2: Coefficient of interaction between indicator of DMP alone and indicator of Month 12 visit = 0), DMP plus M-POWER vs. usual care (Null Hypothesis 3: Coefficient of interaction between indicator of DMP plus M-POWER and indicator of Month 12 visit = 0), and DMP plus M-POWER vs. DMP alone (Null Hypothesis 4: Coefficient of interaction between indicator of DMP alone and indicator of Month 12 visit = Coefficient of interaction between indicator of DMP plus M-POWER and indicator of Month 12 visit). If the missing data patterns do not necessitate using a general linear model for repeated measures as a primary analysis, this analysis will be conducted as a sensitivity analysis.

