#### Secondary outcomes and hypotheses

We will test for differences between groups in mean change in HbA_1c_ levels from baseline at Months 6, 18, and 24. We will also test mean differences between groups for changes in weight and blood pressure, proportion of participants who progress to insulin, self-reported physical activity, weight monitoring, blood glucose monitoring, medication adherence, diabetes self-management, sleep quality, work productivity, daily activity impairment, and health utility index at all four time points (Months 6, 12, 18, and 24). All outcomes will be tested with the hypothesis that improvements will be greatest in the DMP plus M-POWER arm, followed by DMP, followed by usual care.

We will also test potential effect modifiers, including duration of T2DM, baseline HbA_1c_ level, previous or existing experience with mobile apps to manage health conditions, and number of diabetes medications. We hypothesize that those with a longer duration of T2DM, no experience with health management apps, and more diabetes medications will be less successful in improving the primary outcome.

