### Sample size

Data from Bilger et al. [31] showed a standard deviation (SD) of HbA_1c_ levels averaged across usual care and intervention groups being 1.2% at both baseline and after a 6-month intervention and a correlation of 0.4 between the two time points. We assume an SD of 1.2% in HbA_1c_ at Month 12 (primary endpoint) and a correlation of 0.2 between baseline and Month 12 measurements. In order to detect a mean difference of 0.5% between the usual care and DMP arms and 0.5% between the DMP and DMP plus financial incentive arms, with analysis of covariance (ANCOVA) adjustment for baseline HbA_1c_ and multiplicity adjustment by the closed testing procedure [32], a sample size of 90 per group is needed to have 80% power at a two-sided 5% familywise type 1 error rate. To allow for 20% attrition at Month 12, we will recruit 113 patients per arm, or 339 in total.

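### The primary HbA1c models omit two baseline variables that the protocol expects to go with less improvement, so some available precision may go unused

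*Protocol article*

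**What the plan says.** **Primary model.** Under Primary analysis, Month 12 HbA1c is regressed on continuous baseline HbA1c, two arm indicators and "indicator variables for stratification factors (gender and diabetes center) as independent variables will be performed". The third stratification factor, dichotomized baseline HbA1c, enters only in a sensitivity analysis. If drop-out differs between arms, a repeated-measures model of HbA1c at baseline, Month 6 and Month 12 takes over. It adjusts for visit, gender and diabetes center.

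**Predictions about the outcome.** Under Secondary outcomes and hypotheses, four variables are introduced as possible modifiers of the effect: duration of diabetes, baseline HbA1c, experience with health apps, and number of diabetes medications. The authors then predict that "those with a longer duration of T2DM, no experience with health management apps, and more diabetes medications will be less successful" on the primary outcome.

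**Sample size.** The calculation uses "analysis of covariance (ANCOVA) adjustment for baseline HbA_1c" and no other covariate, with "a correlation of 0.2 between baseline and Month 12 measurements". It concludes that "a sample size of 90 per group is needed to have 80% power at a two-sided 5% familywise type 1 error rate".

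**Other adjustment.** Under Quantitative outcomes (secondary analyses), additional analyses are to account for medication changes, effect modifiers, mediators, covariates and engagement metrics. No model is named.

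**The concern.** The protocol expects two characteristics, duration of diabetes and number of diabetes medications, to go with less success on the primary endpoint. Testing that prediction requires their baseline values for everyone. Both are nevertheless absent from a covariate list that the article states in full.

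In a randomized trial with a continuous outcome, pre-specified adjustment for a prognostic baseline variable narrows the confidence interval without biasing the treatment comparison. The planning correlation leaves room for this: at 0.2, baseline HbA1c accounts for 0.2² = 4% of the Month 12 variance. What is at stake is the width of the intervals for the three pairwise comparisons of arms.

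The additional analyses do not fill the gap. They sit under the secondary outcomes and mix baseline variables with post-randomization ones such as medication changes and engagement.

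**Working it through.** **Inputs from the Sample size section**

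- Difference: the trial is to "detect a mean difference of 0.5% between the usual care and DMP arms and 0.5% between the DMP and DMP plus financial incentive arms".
- SD at Month 12: 1.2. Baseline to Month 12 correlation: 0.2.
- Completers per arm: 90. Two-sided level 0.05, with "multiplicity adjustment by the closed testing procedure".
- Attrition: 20%.

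**Step 1. Reproduce the stated figure**

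- Residual SD = 1.2 × √(1 − 0.2²) = 1.176.
- Normal approximation: n = 2 × (1.960 + 0.842)² × 1.176² / 0.5² ≈ 87 per arm. Ignoring the correlation gives 91. The stated 90 lies between them.
- SE of a pairwise difference at 90 per arm = 1.176 × √(2/90) = 0.1753. Noncentrality = 0.5 / 0.1753 = 2.853. The model has six coefficients, so the residual degrees of freedom are 270 − 6 = 264. Noncentral-t power = **81.1%**.
- A simulation of the closed test (200,000 runs, arm means 0, −0.5, −1.0) gives 81.2% for each adjacent comparison. The global test rejects in more than 99.9% of runs, so here the pairwise t-test is an adequate stand-in.
- Recruitment: 90 / 0.8 = 112.5, rounded up to 113; 3 × 113 = 339.

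The plan's figures therefore hold with baseline HbA1c as the only covariate.

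**Step 2. Add two covariates**

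Let R² be the share of the residual variance that the two variables explain jointly. The documents give no value, so a range is assumed.

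- Residual SD becomes 1.176 × √(1 − R²).
- Residual degrees of freedom become 262.
- Chance imbalance in two covariates inflates the variance of a contrast by about 1 + 2/261 = 1.0077.
- SE = residual SD × √(2/90 × 1.0077).

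| Assumed R² | Residual SD | SE | Noncentrality | Power |
|---|---|---|---|---|
| Current model | 1.176 | 0.1753 | 2.853 | 81.1% |
| 0% | 1.176 | 0.1759 | 2.842 | 80.8% |
| 2% | 1.164 | 0.1742 | 2.871 | 81.6% |
| 5% | 1.146 | 0.1715 | 2.916 | 82.8% |
| 10% | 1.115 | 0.1669 | 2.996 | 84.7% |

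The two covariates break even when (1 − R²) × 1.0077 ≈ 1, that is at R² of about 0.8%.

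**Step 3. Sensitivity to the baseline correlation**

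The Sample size section also reports a correlation of 0.4 between baseline and 6 months in the earlier trial it draws on. At 0.4, residual SD = 1.2 × √(1 − 0.16) = 1.100, SE = 1.100 × √(2/90) = 0.1640, and power under the current model is already about 86%. Whether 0.4 would hold at Month 12 is unknown.

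**The case against.** The strongest reply is that this is a preference for a longer covariate list, since the plan contains no error here. Most of its parts stand.

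- **Modifier or prognostic factor.** The protocol introduces these variables as possible effect modifiers. A modifier need not predict Month 12 HbA1c within arms, and only within-arm prediction buys precision. This stands as a caution. The directional prediction, however, concerns success on the primary outcome and is not limited to the intervention arms, so a prognostic reading of duration and medication count is open.
- **Lost precision.** A reader might infer that precision already paid for is thrown away, or that the trial is short of power. The documents do not support this: the sample size counts on baseline HbA1c alone and reproduces on that basis.
- **Bias.** A reader might infer that chance imbalance in the omitted variables biases the primary estimate. It does not; randomization makes the estimator unbiased, and its standard error already allows for such imbalance.
- **A longer list.** A reader might want BMI and app experience added too. The protocol makes no prognostic claim for BMI; it links weight reduction, not baseline BMI, to HbA1c. App experience may only modify the effect of an app-based package, and the article gives no reason for it to predict HbA1c under usual care.
- **Cost-effectiveness.** A reader might carry the imprecision over to the ICER. The article does not say that its denominator comes from this regression.
- **Size.** No document figure supports any value of R². At 2% the gain is half a percentage point of power.

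What the reply does not remove is that the covariate list is fixed in the text, the two variables are tied there to the primary outcome, and adjusting for them costs almost nothing.

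**Conclusion.** The point holds as an optional efficiency improvement of low severity. It is not an error, a bias or a power shortfall.

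The omission itself is certain; the size of the gain is not. With 90 completers per arm, SD 1.2 and correlation 0.2, the change in power for a 0.5-point difference runs from a loss of about 0.3 points (R² = 0) to a gain of about 0.5, 1.7 or 3.6 points (R² = 2%, 5% or 10%). If the baseline correlation is nearer 0.4, power is already about 86% and there is less to gain. The result assumes a linear relation between the two variables and HbA1c, and baseline values that are nearly complete. The article does not say how duration is recorded.

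**What to change.** Make the change in the protocol or the analysis plan while arms are still masked. The article says that a detailed plan will precede the final database lock and that assignments are disclosed only afterwards, so there is time.

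1. In the primary linear model, add duration of type 2 diabetes and number of diabetes medications, both as recorded at baseline.
2. In the repeated-measures model, add the same two variables with covariate-by-visit terms. Baseline HbA1c is one of the outcomes there, so a single coefficient common to all visits would not reproduce the adjustment made in the linear model.
3. Fill missing baseline values by a simple rule that ignores arm, such as the overall mean or a missing category, so that nobody is dropped.
4. Keep the present model as a sensitivity analysis, and keep effect-modifier tests separate.

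The cost is a few lines of text, two degrees of freedom out of 264 in the linear model, and about 0.3 points of power if neither variable is prognostic. No new patients are needed.

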#### Participant withdrawal and discontinuation

Participants are free to withdraw from the study at any time by informing the study team or the investigators of their decision to withdraw. Data that has been collected until the time of their withdrawal will be stored and analyzed. Participants may be discontinued from the study due to one or more of the following reasons:
They become pregnant.Upon voluntarily informing their doctor that they are participating in this study, their doctor decides that continuing participation could be harmful and informs us in the process.They fail to follow the instructions of the study team or investigators.

Participants who develop any of the exclusion criteria 2–13 during the course of the study will not be withdrawn from the study unless they choose to withdraw voluntarily. There are no concomitant care or other interventions that will be prohibited during the study.

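### The default primary analysis is complete-case and ignores Month 6 HbA1c; the more robust repeated-measures model already written in the protocol should be primary without conditions

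*Protocol article*

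**What the plan says.** Protocol article, Primary analysis: the default is a linear regression of Month 12 HbA1c on baseline HbA1c, two arm indicators, gender and diabetes center. It is run in a "modified intention-to-treat population, including participants who have both baseline and Month 12 HbA_1c_ level data". A global test and three pairwise tests follow, and a pairwise null is rejected only if the global test is significant as well.

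The same section then states the exception: "If there are substantially different drop-out rates or different drop-out patterns among the three arms, a general linear model for repeated measures" becomes the primary analysis. That model takes baseline, Month 6 and Month 12 HbA1c as outcomes, has arm-by-visit terms but no arm main effect, and uses an unstructured covariance. Its four null hypotheses are written out. Gender and center enter without visit interactions. If the exception is not triggered, the model is run as a sensitivity analysis.

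Preliminary descriptive analyses: drop-out in each arm is examined by a statistician blinded to assignment, arms are disclosed after final database lock, and "A detailed statistical analysis plan will be prepared before the final database lock".

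**The concern.** The default discards information that the trial collects on the people it loses. A participant seen at Month 6 but not at Month 12 contributes nothing to the headline estimate, although Month 6 HbA1c is probably the best available predictor of the missing value. If drop-out depends on Month 6 response, and does so differently by arm, completers are no longer comparable between arms, even when the arms lose the same number of people.

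The trial's own payments make this plausible. In the rewards arm, each follow-up assessment pays 60 or 30 bonus M-Points according to HbA1c or weight result (Table 2). The other two arms receive fixed payouts of SGD150 and SGD70 for completing Months 12 and 24, whatever the result (Table 3). In the intervention arms, participants can see their assessment HbA1c in the app. A rewards-arm participant with no improvement at Month 6 therefore has less to gain by returning.

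The repeated-measures model handles drop-out that depends on observed HbA1c, but it becomes the headline only if someone recognises a difference between arms in a small number of drop-outs.

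**Working it through.** **The plan's own figures.** The inputs in Sample size are "We assume an SD of 1.2% in HbA_1c_ at Month 12 (primary endpoint) and a correlation of 0.2 between baseline and Month 12 measurements", a difference of 0.5, 80% power and two-sided 5%.
- Adjusted SD = 1.2 × √(1 − 0.2²) = 1.176.
- n per arm = 2 × (1.960 + 0.842)² × 1.176² / 0.5² = 87 (88 with the t distribution). The plan states 90, which gives 81.4% power.
- 90 / 0.80 = 112.5, hence 113 per arm and 339 in total. The plan's figures reproduce.

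**Who is left out.** 113 × 0.20 ≈ 23 per arm; 339 × 0.20 ≈ 68 overall.

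**Size of the bias.** Assumptions not in the document: correlations of 0.4 (baseline–Month 6) and 0.6 (Month 6–Month 12), and the drop-out mechanism. The 0.2 (baseline–Month 12) and the SD of 1.2 are the plan's, with 1.2 applied at all three visits. No true effect. Let D = Month 6 minus baseline; non-response is D ≥ 0, half of each arm. One arm loses 30% of non-responders and 10% of responders; the others lose 20% regardless.
- SD of D = 1.2 × √(2 × (1 − 0.4)) = 1.315. The mean of each half is ±1.315 × 0.798 = ±1.049.
- Completers in that arm: 0.45 responders and 0.35 non-responders, 0.80 in all. Mean D = 1.049 × (0.35 − 0.45) / 0.80 = -0.131, that is, Month 6 shifted by -0.066 and baseline by +0.066.
- Regression of Month 12 on both: Month 6 slope (0.6 − 0.4 × 0.2) / (1 − 0.4²) = 0.619; baseline slope (0.2 − 0.4 × 0.6) / 0.84 = -0.048.
- ANCOVA (baseline slope about 0.2) leaves a bias of -0.066 × (0.619 + 0.048 + 0.2) ≈ -0.057, about 11% of the 0.5 design difference.
- With 40% and 10% (25% lost in that arm): mean D = 1.049 × (0.30 − 0.45) / 0.75 = -0.210, half is 0.105, and the bias is -0.105 × 0.867 = -0.091.

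Simulation with 113 per arm agrees: -0.058 for 30/10, against about 0 when Month 6 is used, with the SD of the estimate 0.175 against 0.170.

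**Error rates under the plan's closed test**

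| Drop-out in one arm | Bias | Familywise error |
|---|---|---|
| 30% / 10% | about -0.06 | 5.7–5.9% |
| 40% / 10% | about -0.09 | 7.5–8.1% |

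**Would the pattern be noticed?** Suppose drop-out is cross-tabulated with Month 6 response (about 56.5 per cell, everyone having a Month 6 value), and the affected arm is compared with one other at the 5% level.
- 30/10: SE = √(0.3×0.7/56.5 + 0.1×0.9/56.5 + 2×0.2×0.8/56.5) = 0.105; z = 0.20 / 0.105 = 1.91; power Φ(1.91 − 1.96) ≈ 48%.
- 40/10: SE = 0.107; z = 0.30 / 0.107 = 2.80; power ≈ 80%.

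So even a well-aimed check misses the milder pattern about half the time. A check on rates alone has nothing to find at 20% in every arm.

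**When there is no harm.** With the same response-dependent drop-out in all arms and true effects of -0.5 and -1.0, completers give -0.498 and -0.995. Under completely random drop-out, global type I error is 4.7% for completers and 4.6% for a switch triggered by a range in drop-out above 10 points.

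**The fallback model's own gap.** Take a null example in which gender affects only Month 12 (0.6 points) and drop-out is 35% against 5% by gender in one arm and 20% in the other. ANCOVA is unbiased, but the protocol's repeated-measures model gives -0.044, because gender has no visit interaction.

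**The case against.** The case for the plan is substantial, and most of it stands.

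- A reader might infer that the primary method is chosen post hoc. It is not. Both models, the hypotheses, the direction of the switch and the role of the unused model are written in advance. The choice rests on drop-out, not on the effect, and is made blinded.
- A reader might see a conflict with Participant withdrawal and discontinuation: "Data that has been collected until the time of their withdrawal will be stored and analyzed". There is none. The repeated-measures model is always run, as primary or sensitivity analysis, and Month 6 HbA1c is a secondary outcome. Nothing promises that these data enter the primary model.
- The trigger covers patterns as well as rates. In the examples above the pattern does differ, and if that is recognised the plan uses the better model. The bias reaches the headline only when it is missed, and the larger pattern is the easier one to see.
- Unadjusted pairwise error rates overstate the harm, since the plan requires the global test to be significant too.
- It is tempting to call the repeated-measures model valid wherever the ANCOVA is. As written, without stratum-by-visit terms, it is not. It also recovers nothing for participants lost before Month 6.
- The threshold may be set in the analysis plan, which is not shown. Its absence from the article is therefore not the finding.

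What remains is that the article itself fixes a complete-case default and holds the more robust model in reserve.

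**Conclusion.** The point holds as a weakness of the default, not as an invalid plan. In the scenarios examined, a bias of about -0.06 to -0.09 points in favour of the arm that loses its non-responders, with familywise error of about 5.7–8.1%, can reach the headline result. That requires three things together: drop-out related to Month 6 response, a relation that differs by arm, and a trigger that is not pulled. The figures rest on assumed correlations and drop-out probabilities; with a common mechanism in all arms the bias is nil. Reporting the repeated-measures result as a sensitivity analysis would show a discrepancy but would not change the confirmatory test. Cheap improvement, not must-fix.

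**What to change.** Make the repeated-measures model in Primary analysis (baseline, Month 6 and Month 12; unstructured covariance; no arm main effect) the unconditional primary analysis in all randomized participants with a baseline HbA1c. Let the gender and diabetes center effects vary by visit. Keep the complete-case ANCOVA as a sensitivity analysis and delete the drop-out-triggered switch.

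The cost is wording only: both models are already planned and the data are already collected. The 113 per arm can stay. Power for a 0.5 difference lies between 81.4% (90 Month 12 values per arm and nothing recovered) and 89.2% (upper bound, all 113 informative: 0.5 / (1.176 × √(2/113)) = 3.20, and Φ(3.20 − 1.96) ≈ 0.89). The small downside is a slightly less simple headline model.
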